# Effectiveness and safety of Daixie Decoction granules combined with metformin for the treatment of T2DM patients with obesity: study protocol for a randomized, double-blinded, placebo-controlled, multicentre clinical trial

**DOI:** 10.1186/s13063-023-07301-4

**Published:** 2023-04-19

**Keywords:** Daixie Decoction granules, T2DM with obesity, Evidence-based clinical trial, Traditional Chinese medicine, Protocol

## Abstract

**Background:**

Type 2 diabetes mellitus (T2DM) with obesity is a glycolipid metabolism disorder, which makes hypoglycaemic treatment more complex and increases the proportion of multidrug combinations. In addition, patients are more prone to adverse reactions and gradually lose compliance with treatment. Previous clinical trials have demonstrated that Daixie Decoction granules (DDG) can reduce body weight and blood lipids and improve the quality of life of T2DM with obesity. But there are a lack of further evaluations for the efficacy and safety of DDG combined with metformin.

**Methods/design:**

The study is designed as a multicentre, randomized, double-blind, placebo-controlled clinical trial. Participants who meet the Nathrow criteria will be randomly assigned to the intervention group and control group (*n*
_1_ = *n*
_2_ = 133). Based on a unified diet control and exercise therapy, the intervention group will be treated with DDG and metformin, and the control group will be treated with DDG placebo and metformin. All subjects will receive a 6-month treatment followed by a 6-month follow-up. Effective rate of a 1% decrease in HbA1c and 3% decrease in body weight will serve as the primary outcome. The secondary outcome include fasting plasma glucose, blood lipids, C-peptides, insulin, inflammatory factors, insulin resistance index (HOMA-IR) and the subcutaneous and visceral fat content in the upper abdomen measured by MRI. Blood routine, urine routine, stool routine, liver and kidney function, EKG and other safety indicators and major adverse reactions were monitored during total treatment and follow-up time.

**Discussion:**

We aimed to determine the efficacy and safety of DDG combined with metformin for the treatment of T2DM patients with obesity.

**Trial registration:**

Trial registration: ChiCTR, ChiCTR2000036290. Registered 22 August 2014,  http://www.chictr.org.cn/showprojen.aspx? proj=59001

## Strengths and limitations of this study

Previous exploratory studies have confirmed that Daixie Decoction granules can reduce plasma glucose, body weight and blood lipids.Based on a previous clinical study, the clinical effect of Daixie Decoction granules combined with metformin in the treatment of T2DM with obesity will be observed using a multicentre randomized controlled double-blind method.Randomization and arrangement to distribute drugs will be applied by the centre, and the placebo will be prepared in uniform by manufacturer of Daixie Decoction granules to ensure that researchers and patients do not have direct contact with the drug preparation and delivery process.We will objectively evaluate the efficacy of the intervention based on the aspects of blood lipids, blood sugar, insulin resistance and chronic inflammatory state and comprehensively analyse the benefits of intervention for type 2 diabetes patients with obesity.Our experiment will be conducted in four centres in the same region of China, and it is uncertain whether similar effects will occur in other regions and races.

## Introduction

In the past 30 years, China’s economy has developed rapidly. The change in people’s lifestyle to a sedentary lifestyle and high-energy/high-fat diet has directly led to an increase in the number of people with type 2 diabetes and obesity [1]. The prevalence of type 2 diabetes among adults in China has increased rapidly from 0.67% in 1980 to 10.9% in 2013, making it the country with the largest number of diabetic patients. It is estimated that diabetes-related medical costs in China reached $110 billion in 2017, representing a huge economic burden [2].

The prevalence of obesity in China increased from 5.7% in 2010 to 6.3% in 2017, and waist circumference also increased significantly from 80.2 cm in 2007 to 83.2 cm in 2017 [3]. Weight gain is an independent risk factor for T2DM [4]. Studies have suggested that increased body weight or waist circumference can aggravate insulin resistance and increase the risk of T2DM and the difficulty of plasma glucose control [5-7]. Compared with those with simple obesity, people with T2DM and obesity have a more difficult time losing and maintaining weight. First, insulin inhibits fat decomposition and promotes fat synthesis, and insulin levels in obese patients increase significantly [8]. Second, the synergistic effect of obesity and T2DM in other metabolic abnormalities can aggravate insulin resistance in T2DM, and the increase in visceral fat may represent the main cause of insulin resistance in obese patients [9]. Weight loss can improve insulin resistance and reduce plasma glucose and risk factors for cardiovascular disease. Controlling weight is an important intervention strategy for T2DM complicated with obesity [10].

Hypoglycaemic therapy for T2DM with obesity is also more complex [11]. Obesity-induced insulin resistance makes it difficult to reach the plasma glucose standard. If improper treatment leads to continuous weight gain, insulin resistance will be further aggravated, so it is necessary to increase the dosage or other types of drugs accordingly to maintain the stability of plasma glucose [12]. When a greater proportion of multidrug combinations is used in treatment, adverse reactions are more likely, and patients exhibit reduced compliance with treatment [13]. The purpose of treatment is not only to control plasma glucose but also to prevent complications, improve the quality of life and save lives [14]. The greatest threat to T2DM patients is complications associated with large vessels, namely, coronary atherosclerosis and stroke [15]. Therefore, for T2DM patients with obesity, how to achieve standard plasma glucose levels to avoid macrovascular and microvascular complications, effectively reduce body weight and reduce the occurrence of obesity-related hypertension, hyperlipidaemia and stroke are clinical problems that must be solved.

Traditional Chinese medicine compounds have the characteristics of multicomponent, multilink and multichannel action, have a variety of pharmacological effects and play a therapeutic role in many key links of diseases [16]. DDG has become department cipher prescription based on long time clinical verification (specific prescription: *Atractylodes lancea* 18 g, *Atractylodes macrocephala* 18 g, *Salvia miltiorrhiza* 15 g, *Polygonum cuspidatum* 12 g, Folium ilicis cornutae 15 g, *Scutellaria* 12 g, *Linderae radix* 9 g). In our previous clinical studies, 80 subjects of T2DM with obesity were recruited, and the intervention treatment of traditional Chinese medicine DDG combined with metformin was conducted for 13 weeks using self-controlled experimental study methods before and after. The results showed that after 13 weeks of intervention, patients exhibited increased weight loss; glycosylated haemoglobin, fasting plasma glucose (FPG) and postprandial plasma glucose levels were decreased; triglycerides, low-density lipoprotein and free fatty acid levels were improved; and high-density lipoprotein levels were increased. DDG also improves insulin resistance in patients, reduces body weight and blood lipids while lowering glucose levels, improves the quality of life of patients and plays roles in comprehensive prevention and treatment. More importantly, during the 13-week intervention, no serious adverse effects were detected. And only 2 cases had adverse effects of diarrhea, and all completed the trial. The relevant achievements have been patented (Application No. 201710563974.4) and are now in the stage of substantive examination.

Therefore, based on a multicentre randomized, double-blind clinical study design, this study aims to sufficiently verify that DDG combined with metformin is effective and safe as an intervention in patients who have T2DM with obesity, laying a foundation for providing valuable new drugs for clinical use.

### Objectives

A preliminary clinical study found that DDG reduces body weight and blood lipids while lowering glucose, improves the quality of life of patients and plays roles in comprehensive prevention and treatment. We attempt to further understand and verify the efficacy and safety of DDG in T2DM with obesity through clinical studies and comprehensively evaluate the benefits of this intervention in patients.

## Methods and analysis

### Study design

The study is designed as a multicentre, randomized, double-blind, placebo-controlled, parallel design clinical trial in which subjects were randomly assigned in a 1:1 ratio to either an intervention (DDG combined with metformin) or a control group (placebo combined with metformin). The random number assignment will be provided by the Clinical Research Center of Longhua Hospital Affiliated to Shanghai University of Chinese Medicine. Participants in each group will receive 24 weeks of treatment and follow-up for 24 weeks after treatment. The study flow chart is shown in Fig. 1.

**Fig. 1 Fig1:**
[figure not shown]
The study flow chart of the whole multicentre RCT

We will record all baseline observations involved during the screening period. During the period of treatment, all participants will be required to record BMI and waist values daily. Routine blood tests, routine urine tests, routine stool tests, and blood biochemistry will be performed and recorded every 3 months. Intraperitoneal fat thickness (imaging MRI measurement of fat layer thickness) will be measured and recorded once each before and after treatment. After the end of the last treatment, all patients will enter the posttreatment follow-up period. All subjects will be followed up once a month. The schedule of participants is shown in Fig. 2.

**Fig. 2 Fig2:**
[figure not shown]
The schedule of participants

### Subject screening and selection

For outpatients or inpatients who come to the hospital, if the diagnostic criteria for type 2 diabetes with obesity are met (as shown in Tables 1 and 2), the inclusion and exclusion criteria will be assessed (as shown below). Patients will not be recruited if any of the inclusion criteria are not met or if any of the exclusion criteria are met. If the patient meets one of the rejection criteria or termination criteria, they will be removed from the trial. Participants will be required to provide written informed consent to cooperate with the doctor’s treatment and follow-up and to provide information that does not exceed the scope of ethical approval. Participants who did not meet the requirements will be removed from the study. During this period, medical history, physical examinations, blood samples and medical records of participants will be collected and kept.

**Table 1 Tab1:** Diagnostic criteria for type 2 diabetes [13]

Standard of diagnosis	Glucose levels in intravenous plasma mmol/L
Typical diabetes symptoms (polydipsia, polyuria, polydipsia, weight loss) plus random plasma glucose testing	≥ 11.1
Fasting plasma glucose test	≥ 7.0
Plasma glucose measured 2 h after glucose load Repeat the test another day for no symptoms of diabetes	≥ 11.1

**Table 2 Tab2:** Diagnostic criteria for obesity [13]

Classification	BMI (kg/m^2^)
- Underweight	< 18.5
- Normal weight	18.5–23.9
- Overweight	24.0–27.9
- Obesity	≥ 28.0
For waist	(cm)
- Male	≥ 90.0
- Female	≥ 85.0

The study aims to recruit 266 participants (4 units in total). The four units include the following major leading and undertaking units. The Longhua Hospital affiliated with Shanghai University of traditional Chinese Medicine, which will recruit 86 participants. The remaining participating units will recruit 60 participants each: Yueyang Hospital of Integrated Chinese and Western Medicine affiliated with Shanghai University of traditional Chinese Medicine; Shanghai Jinshan Hospital of Integrated Chinese and Western Medicine; Shanghai Pudong New District People’s Hospital. Each unit is responsible for the specific responsibilities of the study, including recruiting patients and collecting specimens and data. Laboratory testing and imaging examination will be performed in the corresponding departments of each unit. Data analysis will be performed at the Clinical Research Center of Longhua Hospital affiliated with Shanghai University of Traditional Chinese Medicine.

To ensure the safety of the participants, blinding, data quality, and adherence to the study protocol, personnel directly participating in this study will be completely trained and will follow Good Clinical Practice (GCP) guidelines.

### Inclusion, exclusion and rejection criteria and termination criteria

#### Inclusion criteria

Patients 18–65 years old of any sex;Patients who meet the diagnostic criteria of type 2 diabetes and obesity;Patients who had been diagnosed with type 2 diabetes in the past 12 months, and had not taken any anti-diabetic medication before;After 2 weeks of diet control and exercise therapy, patients whose FPG is greater than 7.0 mmol/L but less than 13.9 mmol/L, and the FPG level does not change more than 2.5 mmol/L before and after the treatment;Patients who agreed to participate in this clinical study voluntarily signed informed consent forms and agreed to participate in all visits and examinations as required by the study protocol.

#### Exclusion criteria [11]

Patients with nephrotic syndrome (urine protein exceeding 3.5 g/L per day), oedema or renal failure (serum creatinine over 115 μmol/L);Patients who have been diagnosed with heart failure (NYHA III-IV) or who have had a pacemaker implanted;Patients with liver dysfunction (aspartate aminotransferase and glutamate pyruvate transaminase levels twofold above the normal range) or a diagnosis of cirrhosis;Patients with high levels of HbA1C (greater than 9%);Pregnant or breastfeeding mothers, including mothers who have given birth within the last 24 weeks;Patients who require insulin therapy;Patients who receive other therapies or whose doses have changed during treatment;Patients with secondary obesity caused by other diseases, such as Cushing’s syndrome, primary hypothyroidism, hypothalamic obesity, polycystic ovary syndrome;Patients who received weight-loss supplements, antidepressants or hormonal medications during the past 3 months and during the study period;Patients with diabetic ketoacidosis or hyperosmolar non-ketoacidosis coma;Patients with an allergy to intervention drugs;Patients with severe hypertension (SBP>160 mmHg, DBP > mmHg);Patients with acute or chronic pancreatitis or pancreatic insufficiency.

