#### Rejection criteria

Those found in the middle of the trial who failed to meet the case selection criteria; failure to complete the diet exercise in accordance with the regulations; failure to use drugs as prescribed, unable to judge efficacy or providing incomplete information; taking drugs that were prohibited and may affect the judgement of the effect.

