#### Termination criteria

Subjects who withdraw informed consent and request withdrawal from the study; pregnancy events occur during the study; side effects of drug or treatment operations are still intolerable; a situation in which the researcher deems it necessary for study withdraw.

If the participant meets the rejection criteria, they are removed, and the data will not be included in the final statistical analysis. However, the termination criteria are related to patients who may terminate during treatment, so the data from these patients will be included in the final statistical analysis.

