### Statistical analysis

#### Population of statistical analysis

##### Full analytical set (FAS)

This term refers to the set including finished and shedding cases but excluding rejection cases. This group includes those who has taken at least one medication and were recorded in at least one follow-up.

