##### Per-protocol set (PPS)

This term refers to cases that meet the inclusion criteria, did not meet the exclusion criteria and completed the treatment plan. In other words, the cases that meet the trial plan, have good compliance and complete the contents prescribed by the CRF will be analysed. PPS will be used to analyse the main indicators for evaluating efficacy and to assess for conformance with FAS results.

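### Participants who start a barred drug or other therapy after randomisation are removed from the trial and the FAS, and two entry exclusions worded to reach into the study period may add to their number

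*Protocol article*

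**What the plan says.** All references are to the protocol article.

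**Who becomes a rejection case.** Rejection criteria lists, among other grounds, "taking drugs that were prohibited and may affect the judgement of the effect" and "Those found in the middle of the trial who failed to meet the case selection criteria".

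**What follows.** Subject screening and selection: "If the patient meets one of the rejection criteria or termination criteria, they will be removed from the trial". The closing paragraph of Termination criteria: "If the participant meets the rejection criteria, they are removed, and the data will not be included in the final statistical analysis". Full analytical set (FAS): "This term refers to the set including finished and shedding cases but excluding rejection cases". The text under Safety analysis set (SAS) bases conclusions mainly on the FAS and fills missing data by LOCF.

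**Entry criteria that reach past entry.** Exclusion criteria contains "Patients who received weight-loss supplements, antidepressants or hormonal medications during the past 3 months and during the study period" and "Patients who receive other therapies or whose doses have changed during treatment".

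**The on-study drug bar.** The section on the placebo combined with metformin group bars other glucose-lowering, lipid-lowering and weight-loss drugs during the trial. It does not name antidepressants or hormonal drugs.

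**The second analysis set.** Per-protocol set (PPS): "This term refers to cases that meet the inclusion criteria, did not meet the exclusion criteria and completed the treatment plan".

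**The concern.** Starting a drug after randomisation is a post-allocation event, and it may depend on how well the assigned treatment is working or tolerated. Deleting those who do so departs from the randomised comparison. It can bias the responder rate (1% fall in HbA1c and 3% fall in weight) if they differ between arms in number or in response.

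Similar participants are also handled differently. Someone who leaves because treatment is ineffective falls under Drop out criteria, and the FAS keeps shedding cases. Someone equally dissatisfied who stays and takes a weight-loss product is deleted.

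The planned check of FAS against PPS cannot expose this, because the PPS leaves the same people out.

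The two entry items add to the difficulty. Conduct during the study cannot be assessed at entry, so writing it into exclusion criteria invites its use later as a ground for rejection.

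**Working it through.** The plan gives no figure for this point, so there is none to reproduce. The check has two parts.

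**1. Tracing the rules for a participant who starts a drug after randomisation**

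- *Weight-loss, glucose-lowering or lipid-lowering drug.* It is barred on study by name. If it may affect judgement of the effect, the prohibited-drug clause of Rejection criteria applies. The participant leaves the trial, the final analysis and the FAS. The exclusion list is not needed for this result.
- *Antidepressant or hormonal drug.* The on-study bar does not name it. The participant is reached if the exclusion wording counts as a prohibition and the drug may affect the effect. The other route is the case-selection clause, if the exclusion item means use in either period or if the item on other therapies applies. Drop out criteria and Termination criteria use the phrase during treatment for study treatment, which supports reading the latter item as reaching past entry.

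So the removal rule is explicit, and the entry wording is at most an additional way into it.

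**2. Possible size of that additional route**

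Inputs from the article: 266 participants, 133 per arm. Assumptions, since the article has no such rates:

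- 1%, 2% or 5% of participants are removed this way: 266 × 0.01, 0.02, 0.05 = 2.7, 5.3, 13.3, taken as 3, 5 and 13.
- There is no true effect, with 40/133 = 30.1% responders in each arm.
- Those removed respond at rate r: the same (30.1%), half (15.0%) or none (0%).

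With a and b removed from the two arms:

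false difference = (40 − r·a)/(133 − a) − (40 − r·b)/(133 − b)

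Example, 9 and 4 removed at half response: (40 − 1.353)/124 − (40 − 0.602)/129 = 0.3117 − 0.3054, or 0.63 points. Example, 13 and 0 removed with none responding: 40/120 − 40/133 = 33.33% − 30.08% = 3.26 points.

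| Removed, a / b | Same response | Half response | No response |
|---|---|---|---|
| 2 / 1 | 0 | 0.12 | 0.23 |
| 3 / 2 | 0 | 0.12 | 0.23 |
| 7 / 6 | 0 | 0.12 | 0.25 |
| 9 / 4 | 0 | 0.63 | 1.25 |
| 3 / 0 | 0 | 0.35 | 0.69 |
| 5 / 0 | 0 | 0.59 | 1.17 |
| 13 / 0 | 0 | 1.63 | 3.26 |

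Entries are percentage points. The arm that loses more low responders looks better, so the direction depends on which arm that is. Removal from one arm only is unlikely in a double-blind trial, and zero response is an extreme case. The table does not size the whole rejection rule, for which the article gives no counts either.

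**The case against.** The strongest reply has four parts.

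- **The entry wording is not the source of bias.** This stands. Rewording the exclusion list alone would remove no bias; the rule that takes rejection cases out of the FAS causes it.
- **The route through the exclusion list rests on a contestable reading.** This stands in part. The *and* between the two periods could require use in both. The case-selection clause is in the past tense and fits entry errors found late. On those readings a new starter is reached through the prohibited-drug clause, which remains explicit.
- **The item quoted first adds almost nothing of its own.** If the neighbouring item on other therapies also reaches past entry, it already catches these users. This stands, so the two items have to be handled together. Trimming only the first would leave the route open, and would delete the only wording that names antidepressants and hormones as barred on study.
- **The size is assumed and small.** This stands for the entry wording. No usage or responder rate is given, and nothing shows that those removed would respond less often.

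A reader might infer that the exclusion wording by itself biases the trial, or that the result will favour the Daixie Decoction granules. The documents support neither. They do not show that starters differ between arms, and the effect may be near nil if starters are balanced.

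The reply does not reach the rule itself. The article states that rejection cases leave the trial, the analysis and the FAS, so this is a stated choice and not a detail left to an analysis plan.

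**Conclusion.** The point holds as a defect in the rejection rule: starting a barred drug or other therapy after randomisation can take a participant out of the trial and out of the analysis on which conclusions mainly rest. The two entry items are a secondary fault. They mix on-study conduct into eligibility and, on one reading, add a small route to rejection, mainly for antidepressant or hormone users.

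The size of the bias cannot be computed from the documents. It is nil if those removed respond like everyone else. For the entry wording alone, under the assumed 1% to 5% removal and 30.1% response, it is nil to about 1 point in plausible cases. The 3.26-point figure needs all 13 removals in one arm and no response among them.

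The change is worth making because it is cheap and restores the randomised comparison for these participants. Confidence is moderate, given the ambiguous wording.

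**What to change.** 1. **Removal rule (the step that reduces bias).** State in Subject screening and selection, Rejection criteria, Termination criteria and Full analytical set (FAS) that a barred drug or other therapy begun after randomisation is a recorded protocol deviation, under both the prohibited-drug and the case-selection clause. These participants continue planned visits, stay in the FAS, and may be left out of the PPS only. Subject screening and selection has to change too; otherwise visits stop and LOCF supplies the later outcomes.
2. **Entry criteria.** Limit both exclusion items to the period before randomisation, so that they can be assessed at entry.
3. **On-study bar.** Move the bar on weight-loss supplements, antidepressants and hormonal medications to the concomitant-drug rule in the section on the placebo combined with metformin group, stated for both arms. Do not simply delete it.

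Cost: a wording amendment to these sections, with no new measurements and only visits already planned. The downside is slight dilution of the effect in the FAS by retained users of drugs that act on weight or glucose. The planned PPS analysis can examine that, and the FAS and PPS comparison would then show what leaving these participants out does.
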